# Safety and validity of extracorporeal fenestration and in situ fenestration in patients with aortic disease involving the left subclavian artery: a prospective, single-center, randomized controlled study

**DOI:** 10.1186/s13063-025-08746-5

**Published:** 2025-01-30

**Keywords:** Aortic disease, Extracorporeal fenestration, In situ fenestration, Thoracic endovascular aortic repair, Randomized controlled study, Study protocol

## Abstract

**Background:**

Thoracic aortic pathologies involving the aortic arch are a great challenge for vascular surgeons. Maintaining the patency of supra-aortic branches while excluding the aortic lesion remains difficult. Thoracic EndoVascular Aortic Repair (TEVAR) with fenestrations provides a feasible and effective approach for this type of disease. The main purpose of this trial is to assess the safety and validity of extracorporeal fenestration and in situ fenestration in patients with aortic disease involving the left subclavian artery.

**Methods:**

This is a prospective, single-center, randomized controlled study. A total of 170 eligible patients will be recruited from The Fourth Affiliated Hospital, Zhejiang University School of Medicine in China and randomized on a 1:1 basis either to the group A (extracorporeal fenestration) or the group B (in situ fenestration). The primary outcome will be the all-cause mortality (30 days). The secondary outcomes will include incidence of secondary intervention (30 days, 6 months, 1 year), incidence of endoleak (30 days, 6 months, 1 year), incidence of major adverse events (MAE) (i.e., immediate procedural success and complications) (30 days, 6 months, 1 year), immediate technical success rate, and all-cause mortality (6 months, 1 year).

**Discussion:**

Suppose extracorporeal fenestration non-inferior to in situ fenestration in patients with aortic disease involving the left subclavian artery. This trial aims to demonstrate the safety and validity of extracorporeal fenestration and in situ fenestration in patients with aortic disease involving the left subclavian artery, which is expected to provide a reference for Thoracic EndoVascular Aortic Repair (TEVAR) with fenestrations.

**Trial registration:**

ClinicalTrials.gov NCT06256757. Registered on February 5, 2024. https://clinicaltrials.gov/study/NCT06256757.

## Administrative information

Note: the numbers in curly brackets in this protocol refer to SPIRIT checklist item numbers. The order of the items has been modified to group similar items (see http://www.equator-network.org/reporting-guidelines/spirit-2013-statement-defining-standard-protocol-items-for-clinical-trials/).

## Introduction

### Background and rationale {6a}

Thoracic aortic pathologies involving the aortic arch are a great challenge for vascular surgeons. Maintaining the patency of supra-aortic branches while excluding the aortic lesion remains difficult. Endovascular repair of the aortic arch using manufactured fenestrated and or branched devices seems to enjoy a satisfactory level of technical success in many cases together with a progressively reduced load in terms of early death [1]. Thoracic EndoVascular Aortic Repair (TEVAR) with fenestrations provides a feasible and effective approach for this type of disease and has gradually become the most used approach in these patients [2, 3]. In situ fenestration as feasible and with a high rate of technical success and satisfactory results in the short term [4–6]. Previous studies suggested that the viability of preserving LSA blood flow in TEVAR using extracorporeal fenestration to treat various aortic pathologies in various clinical situations and the technical feasibility and short-term results that may justify the use of this method in emergency cases [7]. A systematic review and meta-analysis showed favorable short-term results of both extracorporeal fenestration and in situ fenestration techniques with low mortality and strokes rates [8]. But a study demonstrated that the snare double loop reinforcement has an advantage regarding durability of the graft branch assembly. Moreover, non-reinforced fenestrations show signs of weakness and lack of stability, which questions the in situ fenestration procedures [9]. However, most of the previous studies were retrospective, extracorporeal fenestration or in situ fenestration techniques which is the best choice were unknown. The main purpose of this trial is to assess the safety and validity of extracorporeal fenestration and in situ fenestration in patients with aortic disease involving the left subclavian artery.

## Objectives {7}

The main purpose of this trial is to assess the safety and validity of extracorporeal fenestration and in situ fenestration in patients with aortic disease involving the left subclavian artery.

## Trial design {8}

The study design is a prospective, single-center, non-inferiority, randomized controlled trial. A total of 170 eligible participants will be divided randomly into two groups in a ratio of 1:1.

The flowchart of the trial is presented in Fig. 1.

**Fig. 1 Fig1:**
[figure not shown]
Flowchart of the trial

## Methods: participants, interventions, and outcomes

### Study setting {9}

The current study will take place in The Fourth Affiliated Hospital of Zhejiang University School of Medicine in China.

### Eligibility criteria {10}

Inclusion criteria (all of the following criteria were met for enrolment):Patients aged greater than 18 years old and less than 80 years old.Patients diagnosed with thoracic aortic disease, including thoracic aortic dissection, thoracic aortic aneurysm, thoracic aortic ulcer, and intramural hematoma.Patients needed endovascular repair (TEVER).Patients who needed complete coverage of the left subclavian artery (planned landing zone was in zone 2 of the aortic zone).The proximal lesion involved the proximal aorta within 1.5 cm of the posterior edge of the left subclavian artery (LSA) opening, but not the left common carotid artery (LCCA).Suitable femoral artery, iliac artery, and brachial artery access can be used for endovascular treatment.The patients could understand the purpose of the study, volunteered to participate in the study, and informed consent was signed by the subjects themselves or their legal representatives.Patients were willing to undergo follow-up evaluation as required by the study protocol.The life expectancy of the patient is more than 12 months.

Exclusion criteria (if any of the following criteria is met):The lesion involved the proximal aorta of the LCCA opening (zone 0 and zone 1).The patient has a definite connective tissue disease (e.g., Marfan syndrome).The subjects had a history of previous TEVAR.Patients who have had or may have had severe allergic reactions to contrast media (anaphylactic shock, exfoliative dermatitis, etc.).Patients with contraindications to antiplatelet and anticoagulant drugs.The patient’s compliance was poor and the follow-up could not be expected on time.Patients with acute systemic infection.Patients cannot tolerate general anesthesia.Patients judged by the investigator to be ineligible for endovascular treatment.

### Who will take informed consent? {26a}

This trial will be conducted in patients with thoracic aortic disease diagnosed in The Fourth Affiliated Hospital of Zhejiang University School of Medicine from May 2024. All participants included in the trial signed an informed consent form.

### Additional consent provisions for collection and use of participant data and biological specimens {26b}

N/A. No collection or use of participant data or biospecimens was performed.

## Interventions

### Explanation for the choice of comparators {6b}

TEVAR is a feasible and effective approach for aortic disease, which will be implemented in all groups. TEVAR with fenestrations provides a feasible and effective approach for patients with aortic disease involving the left subclavian artery.

### Intervention description {11a}

Eligible patients will be randomized to either the group A (extracorporeal fenestration) or the group B (in situ fenestration). Participants will be done the scheduled endovascular repair which will be performed by surgeons with at least 5 years’ experience. The Chinese expert consensus serves as a technical reference [10].

#### In situfenestration

Left subclavian artery (LSA): From the left brachial artery (LBA), a 6F angle-adjustable sheath (Lifetech, Inc., Shenzhen, China) is introduced retrogradely until its tip reaches the aortic stent graft. The tip is then adjusted to be as perpendicular as possible to the larger curve of the aortic stent graft. Once the sheath gets to the ideal position, a flexible needle (21 gauge, Futhrough, Lifetech, Inc.) is employed to create the fenestration in the aortic stent graft (Ankura, Lifetech, Inc., Shenzhen, China). Following the puncture, a 0.018-inch guidewire (V-18 ControlWire; Boston Scientific, Natick, MA) is inserted through the needle aperture and into the ascending aorta [11–13]. After needle fenestration, the initial aperture is expanded using balloon angioplasty. Deployment of stent in the branch artery.

#### Extracorporeal fenestration

Based on the preoperative CTA reconstructions, the diameter of the aorta and branch vessels, lengths, angles to the arch, clock positions, and related relationships are measured, and a preoperative design for the fenestrations is developed. The outer sheath of the stent graft (Ankura, Lifetech, Inc., Shenzhen, China) is then pushed back for several centimeters under sterile conditions, allowing the proximal portion of the stent graft to be released [14]. The length of the released segment should be 1 to 2 cm distal from the location of fenestration [14]. Using a sterile ruler, the location of the fenestration is determined in accordance with the preoperative plan. The 12 o’clock position is considered to be at the front of the trigger. The position of the stent graft relative to the trigger is also referred to as the 12 o’clock position. If the fenestration must avoid stent struts, then the fenestration is deemed to be at 12 o’clock, as is the position of the trigger relative to the stent graft. The fenestration can be created using scissors or a cautery device. The fenestration can be strengthened using the loop of a snare [14, 15]. To indicate the position of the fenestration during the DSA, either the original mark in the stent graft or an extra marker can be sutured to the fenestration [16]. After passing the aortic arch, the fenestration mark is aligned with the branch artery’s corresponding position. After deployment of the stent graft, a 0.018-inch guidewire is advanced through the fenestration. Deployment of stent in the branch artery.

Follow-up appointments are scheduled at 1, 6, and 12 months after surgery. An aortic CTA will be required for every follow-up.

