### Outcomes {12}

In this trial, the outcomes will be developed according to the standard clinical endpoint of endovascular aortic repair [17]. The primary outcome will be the all-cause mortality (30 days). The secondary outcomes will include incidence of secondary intervention (30 days, 6 months, 1 year), incidence of endoleak (30 days, 6 months, 1 year), incidence of major adverse events (MAE) (i.e., immediate procedural success and complications) (30 days, 6 months, 1 year), immediate technical success rate, and all-cause mortality (6 months, 1 year). All-cause mortality is the annual number of deaths in a given group per the population in that group. Endoleak was assessed by DSA angiography during surgery and by CTA and DUS after surgery. We recommend re-intervening to achieve a proper seal in patients with type I or type III endoleaks following TEVAR according 2024 ESC Guidelines [18]. We recommend to perform 30-day imaging after TEVAR, by CTA and DUS, to assess the success of intervention. A secondary intervention will be performed if necessary, based on the follow-up results and the patient’s condition.

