### Concealment mechanism {16b}

The allocation sequence will be securely stored in sequentially numbered, opaque, sealed envelopes. Once the consent form is completed, the allocation will be revealed to the investigator.

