### Methods for additional analyses (e.g., subgroup analyses) {20b}

Two prespecified subgroup analyses of age (18–49 vs. 50–80) and gender will be conducted for the primary outcome by adding an interaction term (e.g., age × group) into the Cox regression model. A sensitivity analysis will be conducted for the primary outcome based on the per-protocol set, which included patients who adhered to the treatment and follow-ups. Continuous data will be compared using the Student *t*-test or Mann–Whitney *U* test for parametric and non-parametric data, respectively. Categorical data will be compared using the chi-square test or Fisher’s exact test, as appropriate. Since the participants might crossover or be lost to follow-up, non-inferiority will be tested using two analysis sets. One set is the intention-to-treat (ITT) set, which includes all patients as randomized, regardless of whether they received the assigned treatment. The other is the per-protocol (PP) set. *P* < 0.05 will be considered statistically significant, and all data will be analyzed using SAS 9.2 software.

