### Methods in analysis to handle protocol non-adherence and any statistical methods to handle missing data {20c}

The primary outcome will be analyzed according to the modified intent-to-treat principle, which will minimally exclude patients without receiving the assigned treatment or with missing primary outcome data. We propose declaring extracorporeal fenestration non-inferior to in situ fenestration in patients with aortic disease involving the left subclavian artery, only if shown to be non-inferior using both the “intention-to-treat” and “per-protocol” analysis sets.

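### The start of 30-day mortality is not stated, and the modified ITT rule can drop deaths between randomisation and repair that the ITT set is meant to include

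*Protocol article*

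**What the plan says.** All references are to the protocol article.

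- **Endpoint.** Outcomes {12}: "The primary outcome will be the all-cause mortality (30 days", with no starting date. The one definition offered there, "All-cause mortality is the annual number of deaths in a given group per the population in that group", gives no starting date either and describes an annual rate, not a 30-day risk.
- **Clock.** Surgery is the only time origin in the text. The section Extracorporeal fenestration says "Follow-up appointments are scheduled at 1, 6, and 12 months after surgery", and Outcomes {12} says "We recommend to perform 30-day imaging after TEVAR, by CTA and DUS, to assess the success of intervention". These visits line up with the outcome times of 30 days, 6 months and 1 year.
- **Allocation.** Concealment mechanism {16b}: "Once the consent form is completed, the allocation will be revealed to the investigator". This comes before the procedure.
- **Analysis sets.** Methods for additional analyses {20b} defines an ITT set "which includes all patients as randomized, regardless of whether they received the assigned treatment". The section on non-adherence and missing data {20c} allows a non-inferiority claim "only if shown to be non-inferior using both the “intention-to-treat” and “per-protocol” analysis sets". The same section {20c} also says that the primary outcome follows a modified ITT principle, which leaves out patients who did not get their allocated procedure or whose primary outcome is missing.

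**The concern.** Eligible disease includes dissection, intramural haematoma and ulcer, so a death after allocation and before repair is plausible. Such a patient belongs to the ITT set but has no surgery date. If 30 days is counted from surgery, as the visit schedule suggests, the primary outcome is undefined for that patient. So is time zero for the Kaplan–Meier curves and Cox model. The modified ITT sentence goes further: the patient did not receive the allocated procedure and can be removed by rule.

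The per-protocol set holds only patients who adhered to treatment and follow-up, so it cannot contain these deaths. The ITT analysis is the only part of the two-set criterion that can. If the modified set stands in for it, neither part does. A death while waiting for the allocated procedure is part of the outcome of being allocated to it, and with about three deaths expected per arm a few such exclusions matter.

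**Working it through.** **1. The plan's own figure.** Inputs from Sample size {14}: 3.8% mortality in both arms, margin 10 points, two-sided α 0.05, β 0.20 labelled two-sided. The printed formula is n = [2 × 0.038 × 0.962] / 0.10² × (z_α/2 + z_β)² = 7.3112 × (z_α/2 + z_β)².

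- With β halved (z = 1.2816): 7.3112 × (1.96 + 1.2816)² = 76.8, so 77 per group and 154 in total, as stated.
- With z_β as printed (0.8416): 57.4, so 58 per group.

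The stated 77 is thus reproduced with β split in two. Adding 10% gives 154 × 1.10 = 169.4, so 170, or 85 per arm. This point does not dispute that total.

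**2. Weight of one death.** Expected deaths per arm: 85 × 0.038 = 3.23. One death is 1/85 = 1.18 points.

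**3. Effect of uncounted deaths (illustration).** Assumed: 85 per arm and 3 control deaths. The Newcombe upper limit is d + √[(U_T − p_T)² + (p_C − L_C)²], where d = p_T − p_C and U, L are 95% Wilson limits. For control, p_C = 3.53% and L_C = 1.21%.

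| Test-arm deaths | p_T | U_T | d | Newcombe upper limit | Wald upper limit | 10-point margin |
|---|---|---|---|---|---|---|
| 4/85 | 4.71% | 11.48% | 1.18 | 8.3 | 7.1 | met |
| 5/85 | 5.88% | 13.04% | 2.35 | 9.9 | 8.7 | met |
| 6/85 | 7.06% | 14.56% | 3.53 | 11.4 | 10.2 | not met |

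For 6 deaths: 3.53 + √[(14.56 − 7.06)² + (3.53 − 1.21)²] = 3.53 + 7.85 = 11.4.

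Suppose 6 test-arm patients die, 2 of them before repair. Counting all six fails the margin. Removing the two from numerator and denominator gives 4/83 against 3/85, with a Newcombe limit of 8.6, which passes. If only one of five deaths is before repair, the margin is met either way. Starting from 3 deaths in each arm, three extra test-arm deaths are needed to fail (6 against 3).

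**4. Effect of counting them on power.** Assume an equal pre-repair death rate q in both arms, with all these deaths and the 3.8% inside the window. The rate is then r = q + (1 − q) × 0.038, and power at 85 per arm is Φ(0.10/√[2r(1 − r)/85] − 1.96).

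| q (assumed) | r | Power |
|---|---|---|
| 0% | 3.8% | 92.6% |
| 1% | 4.8% | 86.5% |
| 2% | 5.7% | 80.1% |
| 5% | 8.6% | 64.2% |

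**The case against.** **The visit schedule is not an endpoint definition.** This stands. The surgery clock is written for appointments and imaging, and all-cause death needs no visit. A reader might infer that the article itself places deaths before repair outside 30-day mortality. It does not: the origin is unstated.

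**An unstated origin is ordinary SAP detail, and this is a condensed article.** Taken alone, that would be a fair answer. It does not cover the clash between {20b} and {20c}, which are both in the shown text: one keeps untreated patients and the other removes them.

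**Waiting times may not differ.** A reader might also infer that the extracorporeal arm waits longer, because for it "related relationships are measured, and a preoperative design for the fenestrations is developed", while no such step is described for in situ fenestration. The documents do not support that. Both arms use the same stent graft, the fenestration is made under sterile conditions with scissors or cautery, and no ordering time or delay is mentioned. Strategies to improve adherence {11c} promises prompt surgery to an experimental group it does not define. No passage gives a wait for either arm, so neither the size nor the direction of any imbalance is known.

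**The illustration is selected.** Reversal takes two pre-repair deaths in the test arm, none in control, and a 4 against 3 split otherwise. That is correct, and it would be wrong to say that a single lost death changes the result in this example.

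**A plain 30 days from randomisation has its own cost.** It shortens postoperative observation by the length of the wait: a patient repaired on day 20 would contribute only 10 postoperative days. It could also leave the ITT and per-protocol tests on quite different endpoints. This stands and shapes the fix.

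**Conclusion.** The point holds as a gap plus a contradiction. The origin of the primary outcome is not stated, the only clock given is surgery, and the ITT and modified ITT rules conflict on patients who die before repair. Followed as written, {20c} can remove those deaths from the primary result although {20b} says they belong.

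The possible effect is a reversed conclusion if two test-arm deaths go uncounted, assuming 85 per arm, 3 control deaths, 4 other test-arm deaths and a Newcombe or Wald limit. One uncounted death would not do it. The true number of deaths before repair is unknown and may be zero. No bias towards a particular arm is shown.

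**What to change.** In Outcomes {12} and in the section on non-adherence and missing data {20c}, state that:

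- the ITT analysis of the primary outcome includes all randomised patients;
- any death after randomisation and before repair is an event in the allocated arm;
- for repaired patients, the window runs through 30 days after surgery, so that perioperative deaths are still captured;
- ITT survival curves and Cox models start at randomisation;
- the per-protocol analysis and procedural outcomes keep the surgery clock.

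Remove the modified ITT exclusion in {20c}, or reconcile it with the ITT set in {20b}. Set an end date for patients who are never repaired. Record the randomisation and surgery dates and report the interval by arm.

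The cost is wording and two dates. The ITT figure will differ slightly from the usual postoperative 30-day rate, which the per-protocol analysis still gives. Counting these deaths lowers power somewhat, but by the table above it stays at about 80% or more while the pre-repair death rate is no higher than 2% in each arm. Clinical care does not change.

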### Criteria for discontinuing or modifying allocated interventions {11b}

The dropout criteria are as follows: (1) the participants request withdrawal; (2) the investigators consider it inappropriate to continue for safety concerns.

### Strategies to improve adherence to interventions {11c}

The participants in the experimental group will undergo surgical intervention promptly upon admission through research channels, which will help to improve adherence.

### Relevant concomitant care permitted or prohibited during the trial {11d}

Relevant concomitant care or intervention will be determined by physicians based on clinical practice guidelines at their discretion during the trial.

### Provisions for post-trial care {30}

Participants will be compensated for any injuries resulting from trial participation in accordance with the relevant laws of China.

### Outcomes {12}

In this trial, the outcomes will be developed according to the standard clinical endpoint of endovascular aortic repair [17]. The primary outcome will be the all-cause mortality (30 days). The secondary outcomes will include incidence of secondary intervention (30 days, 6 months, 1 year), incidence of endoleak (30 days, 6 months, 1 year), incidence of major adverse events (MAE) (i.e., immediate procedural success and complications) (30 days, 6 months, 1 year), immediate technical success rate, and all-cause mortality (6 months, 1 year). All-cause mortality is the annual number of deaths in a given group per the population in that group. Endoleak was assessed by DSA angiography during surgery and by CTA and DUS after surgery. We recommend re-intervening to achieve a proper seal in patients with type I or type III endoleaks following TEVAR according 2024 ESC Guidelines [18]. We recommend to perform 30-day imaging after TEVAR, by CTA and DUS, to assess the success of intervention. A secondary intervention will be performed if necessary, based on the follow-up results and the patient’s condition.

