### Sample size {14}

The power of the trial is calculated as two co-primary endpoints, sharing a combined *α*-level of 0.05. According to the literature, cumulative 30-day all-cause mortality was similar in both groups: 3.8% [8]. An equal (1:1) equivalence design was used, with *α* = 0.05 (two-sided), *β* = 0.20 (two-sided), Δ = 10%, from which the sample size *n* was estimated. In accordance with the design of the trial and the primary efficacy outcome measures, the sample size was estimated using the following formula:$$n=\frac{\pi_t\times\;\left(1-\pi_t\right)\;+\;\pi_c\;\times\;\left(1-\pi_c\right)}{\left(\mathit\triangle\mathit\;\mathit-\mathit\;\mathit{\left|{\pi_t-\pi_c}\right|}\right)^2}\times\left(\mu_{\mathit a\mathit/\mathit2}\mathit+\mu_{\mathit\beta}\right)^2$$

A minimum of 154 patients (77 per group) will need to be recruited. However, considering a potential dropout rate of 10%, combined with the low probability of adverse events in this trial, the total sample size was expanded to 170 patients.

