### Adverse event reporting and harms {22}

An adverse event (AE) is an untoward medical occurrence in a patient or clinical study subject, which may or may not be caused by the investigational device. All such events, whether expected or not, should be recorded. A severe adverse event (SAE) is an untoward and unexpected medical occurrence or effect that results in death or is life-threatening, explicitly referring to an event in which the subject was at risk of death at the time of the event. It does not refer to an event that hypothetically might have caused death if it were more severe, requires hospitalization or prolongation of existing inpatients’ hospitalization, results in persistent or significant disability or incapacity, or results from a congenital anomaly or congenital disability. All AEs should be reported as following procedures.

An SAE form should be completed and sent by fax or email to the chief investigator within 24 h. All SAEs should be reported to the Research Ethical Committee; the event was “related” (i.e., resulted from the administration of any of the research procedures) and “unexpected” (i.e., an event that is not listed in the protocol as an expected occurrence). Reports of related and unexpected SAEs should be submitted within 15 days of the chief investigator’s awareness of the event, using the NRES SAE form for non-IMP studies. Investigators should report any SAEs as required by Research Ethics Committee, sponsor, and/or Research and Development Office.

The investigator and sponsor will do their best to prevent possible injury caused by the design of this study. In case of any injury related to this study, the sponsor will bear the corresponding treatment costs and make compensation by national laws and regulations. If an adverse event caused by the investigational compression treatment causes harm, the clinical research institution and the investigator will provide timely and adequate treatment and management according to the routine clinical treatment.

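### Three definitions are wrong as written: mortality is defined as an annual figure although the outcome is at 30 days, MAE includes procedural success, and an SAE must be unexpected

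*Protocol article*

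**What the plan says.** **Mortality.** Outcomes {12} makes 30-day all-cause mortality the primary outcome and lists mortality at 6 months and 1 year as secondary. It then gives one definition for all three: "All-cause mortality is the annual number of deaths in a given group per the population in that group". Sample size {14} plans on a different quantity: "cumulative 30-day all-cause mortality was similar in both groups: 3.8"%, with a margin of 10%.

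**MAE.** The same section lists, as a secondary outcome, "incidence of major adverse events (MAE) (i.e., immediate procedural success and complications) (30 days, 6 months, 1 year". The Methods part of the Abstract repeats this definition. Immediate technical success is a separate item in the list.

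**SAE.** Adverse event reporting and harms {22} says of adverse events in general: "All such events, whether expected or not, should be recorded". It then narrows the serious category: "A severe adverse event (SAE) is an untoward and unexpected medical occurrence or effect that results in death or is life-threatening". The next sentence begins by stating what the definition does not cover, namely events that would have been fatal only if worse. It runs on, with commas alone, into hospitalisation, disability and congenital anomaly. An SAE form goes to the chief investigator within 24 hours. For the ethics committee, the text applies two conditions, relatedness and unexpectedness, and explains an unexpected event as one the protocol does not list as expected.

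**The concern.** A non-inferiority margin has meaning only on a stated scale. Here the margin and planning rate are on the 30-day cumulative scale, while the one definition of the outcome is yearly. Applied as written, it gives the same quantity at 30 days, 6 months and 1 year, so three listed outcomes collapse into one.

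The MAE definition mixes a favourable result with unfavourable ones. An arm with more procedural successes would show a higher MAE incidence, which is the wrong direction for a safety outcome. An immediate result also cannot accrue between 30 days and 1 year.

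The SAE definition merges two separate questions: how serious an event is, and whether it was foreseen. Together with the run-on sentence, this can leave serious events unclassified as SAEs and outside the 24-hour form.

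**Working it through.** **1. Mortality: does the planning figure depend on the annual definition?**

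Inputs from Sample size {14}: rate 3.8% in both arms, margin 10%, two-sided alpha 0.05 (z = 1.960), and beta 0.20 labelled two-sided. The printed formula with equal rates is

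n = 2 × p(1 − p) / margin² × (z_alpha/2 + z_beta)²

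- First factor: 2 × 0.038 × 0.962 / 0.10² = 7.311.
- With beta halved, as its two-sided label implies (z = 1.2816): 7.311 × (1.960 + 1.2816)² = 76.8, rounded up to 77. This is the plan's figure.
- With beta = 0.20 not halved (z = 0.8416): 57.4, rounded up to 58, which is not the plan's figure. The use of beta is a separate matter.
- 77 × 2 = 154, and 154 × 1.10 = 169.4, rounded up to 170. This also matches.

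So the trial was sized on 3.8% as a cumulative 30-day proportion. On that scale the plan expects 85 × 0.038 = 3.2 deaths per arm of 85 by day 30. The annual definition plays no part in the calculation, and removing it leaves 77, 154 and 170 unchanged.

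With 12 months of follow-up, the annual sentence most naturally gives deaths in the year divided by group size. That could describe the 1-year outcome. It cannot describe the 30-day or 6-month outcome.

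**2. MAE: no arithmetic is needed.** The connecting term in "incidence of major adverse events (MAE) (i.e., immediate procedural success and complications" is i.e., which introduces a definition. Its two components have opposite meanings, and the first is fixed on the day of the procedure while the incidence is to be reported at three later times.

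**3. SAE: the literal text applied to four kinds of event.**

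| Event | Recorded as AE | SAE as written | 24-hour form as written |
|---|---|---|---|
| Fatal or life-threatening, not listed as expected | yes | yes | yes |
| Fatal or life-threatening, listed as expected | yes | no | no |
| Only disabling, listed or not | yes | no | no |
| Only causing hospitalisation, listed or not | yes | no | no |

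Row two depends on a list of expected events, and the article shows none. Rows three and four follow from the run-on sentence and need no such list.

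**The case against.** The strongest reply is that all three are drafting slips whose intent is plain. The time labels on the outcomes, the cumulative planning rate and the planned Kaplan–Meier curves all point to cumulative mortality at each time. Success inside MAE is probably a slip for failure. Hospitalisation and disability are evidently the rest of a seriousness list damaged by punctuation. Much of this stands: the intent is recoverable, and this is no evidence that the trial was sized on the wrong quantity. But the annual sentence is the only definition of the primary outcome measure, and other text does not steady it: the interim analysis of the primary endpoint is tied to a 6-month assessment, and the sample size section speaks of two co-primary endpoints. The MAE wording appears twice.

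A reader might infer more than the documents support:

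- **That the 30-day rate should be scaled up to a year to show how far the margin is off.** The definition does not ask for this. It would need a constant hazard after surgery, which the documents neither state nor support.
- **That MAE incidence would reach some particular high value.** The documents give no success rate, so any such value is an assumption. The reversed direction is the fault.
- **That procedural success duplicates the listed technical success.** The article uses two terms and defines neither.
- **That expected serious harms would escape expedited reporting to oversight bodies.** The 24-hour form goes to the chief investigator. Ethics reporting already appears tied to related and unexpected SAEs, and stays so after the fix. All adverse events are recorded whether foreseen or not, a data monitoring committee watches safety, and every death counts in the primary outcome.

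**Conclusion.** The point holds as three definitions to correct. The mortality sentence matters most, because it contradicts the time point of the primary outcome and the scale of its margin. It does not alter the sample size: 77 per group, 154 in total and 170 after the allowance for dropout all stand on the cumulative 30-day rate. The MAE definition makes a secondary safety outcome uninterpretable if applied literally; how far it would distort the result cannot be computed from the documents. The SAE definition affects classification and the 24-hour form to the chief investigator. It does not affect the recording of events or the mortality outcome.

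The conclusion rests on reading the text literally. For expected events, it also rests on there being a list of expected occurrences that the article does not show.

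**What to change.** - **Outcomes {12}, mortality:** delete the annual sentence. Define all-cause mortality as the cumulative proportion of patients in the analysis set who have died from any cause by 30 days, 6 months and 1 year.
- **Outcomes {12} and Abstract, MAE:** take procedural success out of the definition so that MAE counts adverse events only, and report success as its own outcome.
- **Adverse event reporting and harms {22}:** remove the word unexpected from the SAE definition. End the sentence on hypothetically fatal events where that idea ends, and list hospitalisation and disability as seriousness criteria. Keep expectedness only as the ethics-reporting criterion that the section already uses.

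The cost is wording in these places, with no new data and no change in sample size. The corrections should be in place before outcomes are analysed.
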